***Primary***	
Psychological Well-Being	Warwick-Edinburgh Mental Well-Being Scale [77]
Depression	Center for Epidemiologic Studies Depression Scale [78]
Self-esteem	Rosenberg Self-Esteem Survey [79]
Quality of Life	Global Quality of Life Scale [80]
***Secondary***	
Personal Growth	Personal Growth subscale of Ryff’s Psychological Well-Being Scales [81]
Purpose in Life	Purpose In Life subscale of Ryff’s Psychological Well-Being Scales [81]
Social Support	Social Provisions Scale [82]
Self-Efficacy	Generalized Self-Efficacy Scale [83]

At their face-to-face interview, participants will undertake a battery of tests to assess their physical health. These will include physical function tests (chest press, seated row, leg extension, chair rise to standing, 400 m walk, 6 m backward walk, 6 m normal pace walk, 6 m fast pace walk [60]), resting heart rate, blood pressure, height, weight, and waist girth. A qualified exercise physiologist will be present at all times, and any adverse events during testing will be managed appropriately and reported to the Ethics Committee as per University requirements. In addition, participants will be interviewed on their attitudes to volunteering and any perceived barriers, motivators, and facilitators relevant to commencing and maintaining volunteering behaviors. During an open-ended interview, participants will be asked about their history with volunteering to control for this potential confound, and their current and historical engagement in physical, mental, and social activity will be assessed to control for the degree to which isolation is mitigated by active memberships in recreational and/or social groups.

All participants will be asked to keep a daily record of their physical activity during the six-month study period, including the nature, duration, and perceived exertion of each physical activity episode. Those in the intervention condition will also be asked to keep a daily record of their volunteering activities, once again including details of the nature, duration, and perceived exertion of each episode.

Participants will be also asked to wear a pedometer and note the daily number of steps and engagement in activity in their activity diaries. Although pedometers are considered generally effective for measuring physical activity among older people [61], they are limited in their ability to measure and quantify the intensity of physical activity or detect periods of sitting or lying, which are critical for the evaluation of sedentary behaviors. All participants will therefore be asked to wear accelerometer-based activity monitors (GT3X+, Actigraph, Pensacola, FL) for 7 days after their first interview and for 7 days before their second interview to measure these outcomes.

The second interview will occur at the end of the six-month study period. Participants will be asked to complete the same battery of measures they completed at baseline. They will then participate in the follow up face-to-face assessment. This follow-up assessment will involve the same protocol as the first, with additional questions relating to volunteering experiences in the intervention group. These questions will include descriptions of the types of volunteering undertaken, their level of satisfaction with and enjoyment of their volunteering activities, and factors such as the level of recognition received and any skills they accrued [62]. A typology of volunteering activities will be developed and used to code responses [63,64]. Relevant barriers, motivators, and facilitators to initial and continuing participation will be assessed. Participants in the control group will also be asked to report on any participation in volunteering activities to assess for potential confounds. Should any adverse events be reported in this follow-up interview, they will be documented and submitted to the University Ethics Committee. Participants in both conditions will be provided with a report on their individual results. Physiological testing and interviewing processes will be managed to ensure that participants in the two groups (control vs volunteering intervention) do not interact with each other. The intervention and control conditions are described below.

#### Intervention

Those assigned to the intervention group will be required to undertake a minimum of 60 min of volunteer work per week. They will be advised that they can undertake any form of volunteering they wish during the study period, as long as it meets the definition of volunteering stated above. Participants will be provided with access to the services of a volunteering service organization to ensure they can select a position they find attractive and fulfilling. This will also assist in ensuring that participants are able to secure and commence their volunteering work in a timely fashion. As previous research has identified the importance of goal-setting in activity initiation [65], the purpose of the discussion with the volunteer organization representative will be to commence the participants’ decision-making processes in relation to the volunteering activity they will undertake. The volunteering representative will be available to provide ongoing support to all participants in the intervention condition throughout the study period. Participants will also have the option of contacting the study coordinators should they have any difficulty sourcing or maintaining volunteer work.

Having a choice of volunteering activity is important given the findings of previous research that flexibility is a key characteristic of successful volunteer programs [66].  Tang et al. [67], for instance, found that over three-quarters of seniors rated the choice of volunteer activities and setting their own schedule as being important. Numerous studies have also noted seniors’ desire to be engaged in pastimes that they find meaningful and rewarding [40,55,68,69]. As such, while seniors will have access to advice relating to potential volunteering opportunities in their local area, the final choice of activity will be theirs.

#### Control

Participants assigned to the control condition will be advised to maintain their existing lifestyles or take on new activities as they see fit. For ethical reasons, those with a sedentary lifestyle at baseline will not be required to maintain this lifestyle over the study period.

An attrition rate of 25 % is expected over the six-month intervention study [70,71]. Participant remuneration and responsive administrative processes (e.g., accessible, friendly staff and flexibility in interview scheduling) are expected to prevent excessive attrition. In addition, the participants will be asked to return their physical activity diaries on a monthly basis, which will facilitate follow-up contact with those who appear to be having difficulty or who may be at risk of withdrawing. The diaries will be user-friendly and require basic information in the form of steps per day, type of activity (e.g., swimming), duration (e.g., 30 min), and intensity (light, moderate, or vigorous). Example entries will be included in the diaries to demonstrate correct completion and to reduce the likelihood of respondent fatigue.

The CONSORT diagram of the study design from recruitment to debrief is presented in Fig. 1.

**Figure 1 Fig1:**
[figure not shown]
CONSORT diagram of the study design

### Outcomes

#### Primary

The primary physical outcomes (dependent variables) will be physical activity (steps taken; time spent in light, moderate, and vigorous physical activity; and sedentary time - measured using pedometers and activity monitors) and physical health (measured using a battery of physical functioning tests, resting heart rate, blood pressure, BMI, girth). The primary psychological outcomes (dependent variables) will be psychological well-being, depression, self-esteem, and quality of life (measured using the questionnaires listed in Table 2). Life satisfaction, assessed via a single-item, will also be a primary psychological outcome. Secondary outcomes will be self-reported personal growth, purpose in life, social support, and self-efficacy (measured using the questionnaires listed in Table 2), and attitudes to volunteering (assessed via open-ended interview and an amended version of the Community Service Attitudes Scale [72]).

### Analysis

#### Quantitative analyses

Analyses will be conducted using the intention-to-treat principle, based on all randomized participants. Despite randomization, baseline differences in groups may still occur due to chance. Similarity of baseline characteristics of intervention and control participants will therefore be assessed using appropriate descriptive statistics and inferential analyses (e.g., independent samples *t*-tests, Mann Whitney *U* tests, Pearson’s chi-square statistic, ANOVA). Baseline data will be also examined to analyze systematic bias in attrition.

##### Primary analyses

The primary analyses will utilize a between groups design with two time points (baseline and post-intervention) and two groups (volunteer vs. control). The primary independent variable is therefore condition. Relevant analyses (e.g., multivariate analyses of covariance) will be performed to explore pre to post differences in measures of physical and psychological health while controlling for baseline scores on those variables and any other relevant confounders (e.g., control group members engaging in increased physical activity because recommended to do so by their medical practitioners). An alpha level of *p* < .05 will be the criterion for significance in all statistical comparisons. Estimates of effect size will also be calculated.

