### Volunteering

Volunteering is defined as work activities that are unpaid, non-compulsory, and unrelated to family obligations [18]. ABS [19] data indicate that around a third of Australians engage in some form of volunteering within a 12-month period, with the highest rates among those aged 55–64 years (46 %) and 65–74 years (38 %). Previous studies suggest that volunteering has substantial health benefits for older people (for reviews see [20-22]). While causality is difficult to demonstrate due to the largely observational nature of data synthesized in reviews, evidence suggests that engaging in volunteering activities may provide beneficial social, physical, and cognitive outcomes for older people [23-32].

Volunteering has also been linked with higher levels of self-rated health, lower mortality rates, reduced risk of depression, and improved psychological well-being [20,30,33-38]. One of the mechanisms by which health benefits are produced by volunteering may be an increase in physical activity [39], which is likely to be largely due to additional manual work and walking [29]. However, there is a lack of physical evidence of this relationship, and little understanding of why it exists [31] and which forms of volunteering are most effective in generating positive health effects [40].

Motivational studies consistently demonstrate that an advantage of volunteering is that it gives older individuals an increased sense of meaning [24,41]. In a study of seniors’ conceptions of well-being [42,43], results showed that older people are interested in undertaking activities that are of benefit to others and that volunteering is salient in their deliberations about how they could achieve this outcome. However, a primary barrier was reported to be a lack of knowledge regarding volunteering opportunities and how they can be accessed. There appears to be a preference for word-of-mouth communications about volunteering opportunities, especially in the form of direct invitations to assist with specific tasks [44-46].

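### The only example of a further confounder for the primary analysis is a behaviour that arises after allocation, in the control arm alone; it should not enter the primary model

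*Protocol article*

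**What the plan says.** The primary analysis (Protocol article, Primary analyses) compares volunteer and control groups at follow-up, for instance by multivariate analysis of covariance. The model is to adjust for each outcome's value at baseline. Beyond that, it is to adjust for "any other relevant confounders (e.g., control group members engaging in increased physical activity because recommended to do so by their medical practitioners". The parenthesis is the only illustration given of a further confounder for this model.

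Four other statements bear on it:

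- The aim at the end of the Background is to compare a volunteering programme with usual lifestyle activities.
- The Control section says controls will be "advised to maintain their existing lifestyles or take on new activities as they see fit".
- The Outcomes section states: "The primary physical outcomes (dependent variables) will be physical activity (steps taken; time spent in light, moderate, and vigorous physical activity; and sedentary time".
- The Quantitative analyses section states: "Analyses will be conducted using the intention-to-treat principle, based on all randomized participants".

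No section confines the adjustment to a sensitivity or secondary analysis.

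**The concern.** A confounder of a treatment comparison influences both who receives the treatment and the outcome. Under randomisation nothing that happens after allocation can have influenced allocation, so later behaviour cannot be a confounder of the assigned comparison. Here the proposed covariate is also defined in one arm only. It would remove a subgroup's experience from the control mean while similar people in the volunteering arm stay in theirs.

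What is at stake is the primary estimate for every primary outcome. Activity taken up on a doctor's advice is part of ordinary life for people in this age group, and the control condition allows it. Adjusting it away replaces the declared comparator with a control group in which nobody took such advice. For the activity outcomes the covariate is also partly a function of the dependent variable.

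**Working it through.** The plan gives no figure on this point, so there is none to reproduce. The planned sample size does not depend on it. The check is a reading of timing and definition, followed by an illustration of size.

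**Timing and definition**

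1. Baseline scores are named separately in the same sentence, so the example is not baseline activity under another name.
2. Membership of the control group exists only after allocation, and an increase is a change from an earlier level. The covariate is therefore post-allocation.
3. It is described for controls only. A participant in the volunteering arm who took the same medical advice would not be flagged.
4. The Control section permits the behaviour, so it is part of the comparator and not a departure from it.

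**Size of the shift from a control-only term**

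All inputs are assumptions, since the document gives none. Assignment has no effect on outcome or on uptake. A share p of each arm increases activity, these people gain g (in SD units), and without the activity they would score d SD lower than the others. Set the mean of those who do not take up activity to 0.

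- Mean in each arm: p × (g − d) + (1 − p) × 0 = p(g − d).
- Without the term: p(g − d) − p(g − d) = 0, which is correct.
- With a control-only indicator, the control reference becomes controls who did not increase activity, with mean 0. The estimate is p(g − d) − 0 = p(g − d).

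Positive values favour volunteering. With g = 0.3:

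| p | d = 0 | d = 0.3 | d = 0.5 |
|---|---|---|---|
| 0.10 | 0.10 × 0.3 = +0.03 | 0 | 0.10 × (−0.2) = −0.02 |
| 0.15 | 0.15 × 0.3 = +0.045 | 0 | 0.15 × (−0.2) = −0.03 |
| 0.30 | 0.30 × 0.3 = +0.09 | 0 | 0.30 × (−0.2) = −0.06 |

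**Simulation checks**

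- For p = 0.15, g = 0.3, d = 0 and 150 per arm, a simulation gave 0.043 against the 0.045 from the formula.
- A second simulation used 400 participants, no true effect and no gain from activity. Uptake in controls was set at 10 to 30% for a person of average health, and was more likely in those with poorer unmeasured health. Baseline-only analysis of covariance was centred on zero, with type I error of about 5%. Adding the control-only indicator moved the estimate by about −0.02 to −0.10 outcome units and raised type I error to about 6 to 21%.

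**If the adjustment were extended to follow-up activity in both arms**

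The protocol does not state this model, but the open wording would allow it. The Volunteering section says: "One of the mechanisms by which health benefits are produced by volunteering may be an increase in physical activity". Adjusting for activity in both arms would then also remove whatever benefit acts through activity. With an assumed direct effect of 0.10 and 0.09 through activity, the baseline-adjusted estimate was 0.19. Adding follow-up activity left 0.10, or 0.05 when activity and outcome also shared an unmeasured cause.

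**The case against.** The strongest reply is that both the model and the confounder are introduced as examples. The covariate list would normally sit in an analysis plan that is not shown, and one parenthesis should not be read as a commitment. The Procedure section also shows that the investigators had sensible baseline covariates in mind, since volunteering history and prior activity are asked about at the first interview so that they can be controlled for. It is true that the list is open and that the final model may differ. But an analysis plan can complete a list. Here the published primary analysis states a wrong principle, and it invites further covariates of the same kind.

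A second reply is that no one is excluded or moved between arms, so the intention-to-treat statement, which speaks of all randomised participants, is not literally contradicted. That is right. The difficulty is that the adjusted estimate is no longer the effect of assignment that such an analysis is meant to give.

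A third is that mediation is beside the point, because activity advised by a doctor in controls was not caused by volunteering. That is also right for the example as written. The mediation argument applies only if adjustment is extended to both arms.

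Finally, new activity among controls may be a legitimate interest. It is, but it belongs in description or in a labelled secondary analysis.

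**Conclusion.** The concern stands for the stated example: it should not be a covariate in the primary model. That conclusion rests on timing, on the one-arm definition and on the protocol's own description of its comparator. Bias in the effect of assignment needs only that the increased activity affects the outcome or is related to prognosis, without the two cancelling exactly. Its size and sign rest on the assumptions above: in the central illustration, between +0.045 and −0.03 SD.

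Four stronger readings are tempting and not supported:

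- **That randomisation is broken.** Allocation is untouched; only the adjusted estimate loses its protection.
- **That the adjustment favours volunteering.** This holds if those who take up activity are prognostically average. People advised by a doctor may well be in poorer health, which pulls the shift the other way.
- **That control-arm volunteering will also be adjusted for.** The Procedure section says only: "Participants in the control group will also be asked to report on any participation in volunteering activities to assess for potential confounds". It does not say that these reports enter the primary model.
- **That baseline significance tests will choose the covariates.** The Quantitative analyses section says: "Similarity of baseline characteristics of intervention and control participants will therefore be assessed using appropriate descriptive statistics and inferential analyses". That describes similarity, and nothing there makes the tests a selection rule.

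**What to change.** Delete the parenthetical example. State that the primary model adjusts only for the baseline value of the outcome and for prespecified baseline covariates that allocation cannot have affected, for example age, sex, assessment campus and volunteering history, and that no behaviour arising after allocation enters it.

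The rule should be worded around what allocation could have affected, and not simply as measured before randomisation. The Sample/Randomization section places randomisation after eligibility screening without saying that baseline assessment comes first. The Procedure section has the baseline activity monitor worn for 7 days after the first interview. Baseline activity should therefore serve as a covariate, including as the baseline value for the activity outcomes, only if it is recorded before participants learn their assignment.

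Report new activity and volunteering in controls descriptively by arm, or in a secondary analysis labelled as such.

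The cost is wording only: no new data and no change to the sample size. It should be settled before outcomes are analysed.

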The aim of this study is to assess the relative and combined effects of volunteering on seniors’ physical and mental well-being. This aim will be achieved in the context of a randomized controlled study using an Australian population sample. The primary research objective is to test whether engagement in a volunteering program results in significant improvements to physical and mental health compared to control (usual lifestyle activities). The results can be used to inform public policy on this issue and develop appropriate strategies to encourage older people to participate in volunteer activities.

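### About 22–23 primary outcomes with no lead outcome, all judged at unadjusted p < .05: chance of a false difference up to about 69%, of a false improvement up to about 44%

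*Protocol article*

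**What the plan says.** **Primary outcomes.** The Outcomes section opens the list with activity: "The primary physical outcomes (dependent variables) will be physical activity (steps taken; time spent in light, moderate, and vigorous physical activity; and sedentary time". It adds physical health, "measured using a battery of physical functioning tests, resting heart rate, blood pressure, BMI, girth", then four questionnaire outcomes, and ends: "Life satisfaction, assessed via a single-item, will also be a primary psychological outcome". The function battery is itemised under Procedure, after Table 2: "physical function tests (chest press, seated row, leg extension, chair rise to standing", followed by a 400 m walk and three 6 m walks, eight tests in all. No outcome is named as the lead.

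**Threshold.** The Primary analyses section sets p < .05, which "will be the criterion for significance in all statistical comparisons".

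**Method.** The same section says: "Relevant analyses (e.g., multivariate analyses of covariance) will be performed to explore pre to post differences". It states no order of testing and no global test that must succeed before individual outcomes are read.

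**Objective.** At the end of the Background, the primary objective is to test whether "engagement in a volunteering program results in significant improvements to physical and mental health compared to control". The article does not say which outcomes, or how many, must be significant to support that.

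**Sizing.** The Sample/Randomization section sizes the trial at power 0.80, alpha 0.01 and effect size 0.1, giving 370, raised to 400, with 25% loss expected.

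**The concern.** Many outcomes carry equal primary status, and any of them can be declared significant at the level meant for a single test. An analysis plan could supply missing detail, but this is not a missing detail. The article states one threshold for every comparison, and a later plan that adjusted for multiplicity would contradict it.

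At stake is the main claim. The article says its results should inform public policy and investment in the volunteering sector. With no lead outcome and no rule for success, whichever primary measures fall below .05 can be put forward, and a reader cannot tell how surprising that is if volunteering does nothing.

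**Working it through.** **1. The plan's own figure.** The article gives no familywise error rate. Its one related figure is 370. A two-group by two-time interaction with f = 0.1, alpha 0.01, power 0.80 and an assumed correlation of 0.5 between time points needs 296, and 296 × 1.25 = 370. The match depends on that assumed correlation and on multiplying by 1.25. It is used here only to confirm that 0.01 is plausibly the sizing alpha.

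**2. Counting the primary outcomes.**
- Activity: steps; light, moderate and vigorous time; sedentary time = 5
- Function tests = 8
- Resting heart rate 1, systolic and diastolic pressure 2, BMI 1, girth 1 = 5
- Psychological: four questionnaires plus life satisfaction = 5

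The total is 5 + 8 + 5 + 5 = 23, or 22 if blood pressure is one outcome. If the battery were scored as one measure, the total would be 15–16.

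**3. Error if each outcome is tested at .05 and there is no effect.** Sidedness is not stated. Two-sided tests are assumed, because F-tests such as those in analysis of covariance have no direction. Each test then has 0.05 for a difference and 0.025 for an improvement. Under independence with 23 outcomes:
- any difference: 1 − 0.95^23 = 0.693
- an improvement: 1 − 0.975^23 = 0.441
- expected false differences: 23 × 0.05 = 1.15, of which 23 × 0.025 = 0.575 are improvements

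The article gives no correlations, so a range was simulated (multivariate normal, 400,000 draws, 23 outcomes):

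| Assumed correlation | Any false difference | False improvement |
|---|---|---|
| 0 | 0.69 | 0.44 |
| 0.2 | 0.64 | 0.34 |
| 0.3 | 0.58 | 0.30 |
| 0.4 | 0.52 | 0.26 |
| 0.5 | 0.45 | 0.22 |
| 0.7 | 0.31 | 0.15 |
| Four blocks, 0.3 within / 0.1 between | 0.64 | 0.36 |
| Four blocks, 0.5 within / 0.2 between | 0.57 | 0.30 |
| Four blocks, 0.7 within / 0.2 between | 0.48 | 0.25 |

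With 22 outcomes the independent figures are 0.68 and 0.43. With 15–16 they are 0.54–0.56 and 0.32–0.33.

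**4. Does the sizing alpha solve it?** No. Using 0.01 on all 23 gives 1 − 0.99^23 = 0.21 if independent, and the analysis section uses .05 in any case.

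**5. Price of control.** Completers: 400 × 0.75 = 300. For ANCOVA with an assumed baseline correlation of 0.5, the variance factor is 1 − 0.25 = 0.75. At power 0.80, detectable d = √(4(z_α + z_β)² × 0.75/300) = 0.1 × (z_α + z_β), two-sided:
- alpha 0.05: 0.1 × (1.960 + 0.842) = 0.28
- alpha 0.025 (first Holm step over two): 0.1 × (2.241 + 0.842) = 0.31
- alpha 0.01 (sizing): 0.1 × (2.576 + 0.842) = 0.34
- alpha 0.05/23 = 0.0022 (first Holm step over 23): 0.39

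On the interaction model of step 1, power with 300 completers is 0.81 at alpha 0.01 and 0.64 at 0.0022.

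**The case against.** **The only method named is multivariate.** One joint test per domain would hold the error near 1 − 0.95² = 0.0975 over two independent domains. So testing each outcome separately is an inference. That stands, and the figures above are conditional on it. It does not clear the plan: the method is only an example, nothing makes a joint test a gate, and the threshold covers every comparison.

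**The battery may be one score.** The Outcomes section refers to it as a single battery. No scoring rule is given, and even then 15–16 primary outcomes remain.

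**The objective concerns physical and mental health together.** If a claim needed an improvement in both domains, the independent figure would be (1 − 0.975^18)(1 − 0.975^5), about 4% (about 14% counting either direction). This is a fair reading of the objective, but the article does not state it as a rule.

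**Readings that go too far.** A reader might infer that a trial of an ineffective intervention would more likely than not, or usually, report a false improvement. The article does not support that: the 69% counts both directions under independence, and the improvement figure is below one half in every two-sided case computed. Even for differences in either direction, more likely than not fails once the common correlation passes about 0.4, and several of these outcomes are plausibly related. A reader might also infer that the primary set is unsettled because life satisfaction is missing from the abstract and Table 2. The Outcomes section plainly makes it primary, so this is only a mismatch between lists.

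**Conclusion.** The point holds as a conditional statement. About 22–23 outcomes are primary, none leads, and the stated threshold is unadjusted. If they are tested individually, two-sided, the chance of a false difference is up to about 69% (58% at correlation 0.3, 45% at 0.5), roughly nine to fourteen times the 5% of a single test at the correlations 0 to 0.5. The chance of a false improvement is up to about 44% (30% and 22%), roughly nine to eighteen times the 2.5% of a single test over the same range. Stronger correlation lowers both. The size rests on assumed correlations, assumed two-sided tests and separate testing. The lack of any control follows from the text itself. Because it bears on the main claim and can be cured in wording, it should be corrected before outcome data are analysed.

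**What to change.** Replace the blanket threshold sentence with a rule that controls overall two-sided error at 0.05 across the primary between-group comparisons. Two forms would do:

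- **(a) Lead outcomes.** Name one lead outcome for the physical domain and one for the psychological domain. Test the two by Holm (smaller p-value against 0.025, then the other against 0.05). Report the other primary measures as supportive.
- **(b) Full list.** Apply Holm to all primary outcomes, enumerated in the Outcomes section itself: each function test, systolic and diastolic pressure separately, and life satisfaction included.

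Under either form, make the abstract and Table 2 agree with that list. State whether tests are two-sided and whether any multivariate test acts as a gate. Barring significance claims for secondary outcomes is optional.

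**Cost.** No new data are needed. With 300 completers and a baseline correlation of 0.5, the detectable difference rises from about 0.28 SD to about 0.31 SD under (a). That first step is still looser than the alpha of 0.01 used for sizing (about 0.34 SD), so (a) is affordable within the planned size. Under (b) it rises to about 0.39 SD at the first step, a real loss of power. Form (a) requires the investigators to commit to two outcomes now. The trial is listed as ongoing, and a choice made after the results are seen would not be credible.
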